## Abstract

Mild traumatic brain injury (mTBI) is a prevalent neurological condition, affecting millions worldwide, and frequently resulting in persistent cognitive impairment that significantly impacts daily functioning. Current clinical management and recommendations lack evidence based therapeutic interventions, with treatment approaches limited to symptom monitoring and activity modification. Non-pharmaceutical interventions are needed to promote cognitive recovery and mitigate long-term consequences of mTBI. The goal of this randomized control pilot study is to evaluate the feasibility and preliminary efficacy of a symptom-guided and virtually delivered aerobic exercise intervention for improving cognitive function following mTBI. We are conducting a 12-week pilot randomized control trial of exercise to promote recovery from mTBI, which aims to recruit 24 participants who have suffered an mTBI within the last year and are between the ages of 18–55 years old. Participants are randomly assigned to one of two groups: an intervention group receiving 90 min of virtually-delivered, symptom-guided aerobic exercise weekly for 12 weeks, or a control group receiving 90 min of virtually-delivered balance exercises weekly for 12 weeks. Comprehensive assessments, including cognitive testing and multimodal neuroimaging, were conducted pre and post intervention. We implement physical activity monitoring during weeks 1, 6, and 12 using accelerometry to measure behavior changes. This study will establish the feasibility of virtual exercise delivery in mTBI populations and preliminary evidence regarding cognitive and brain health benefits of aerobic exercise in mTBI. Results will inform future large-scale trials and contribute to an accessible, evidence-based intervention for cognitive recovery after mTBI.

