### Summary of aims

1.1

The primary aim is to establish the feasibility of delivering a virtual exercise intervention in community-dwelling individuals with mTBI, including assessment of recruitment rates, adherence, retention, and safety parameters. The secondary aim establishes precision around the mean and variance [64] of a symptom-guided aerobic exercise intervention to change cognitive function and metrics of brain structure and function following recent (within 1-year of injury) mTBI. Two exploratory aims will investigate: (1) the precision around the mean and variance of aerobic exercise's effect on cognitive function; and (2) the precision around the mean and variance of aerobic exercise's effect on neuroimaging measures of brain structure, function, connectivity, and perfusion. A final exploratory aim is to measure changes in objectively measured daily physical activity and sedentary behaviors measured three times across the intervention period and their associations with neurological and cognitive outcomes.

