**Fig. 1 fig1:**
[figure not shown]
Overall Study Design. Baseline is followed by 12-week intervention period with actigraphy at Week 1, Week 6, and Week 12. After completion, an endpoint visit is conducted.

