### Randomization

2.5

Participants are randomized after the baseline session is complete using a block randomization in block sizes of four and six with equal allocation to each group. Randomization were done in REDcap.

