### Psychosocial assessments

2.11

A battery of questionnaires are administered at baseline and endpoint including quality of life and lifestyle behaviors questionnaires (see Table 2). Additionally, pre-injury behaviors are of interest to see how engagement in healthy lifestyle behaviors pre-injury may contribute to recovery from mTBI. As such, we will administer a modified International Physical Activity Questionnaire (IPAQ), asking specifically about pre-injury physical activity engagement.

**Table 2 tbl2:** Study assessments and timeline.

	Phone Screen	Baseline (in person)	Randomization	Week 6	Week 12	Endpoint (in person)
Prescreening Questionnaire	X					
The Physical Activity Readiness Questionnaire (PAR-Q)	X					
Informed Consent		X				
Demographics		X				
The Ohio State University Traumatic Brain Injury Identification Method (OSU TBI-ID) Questionnaire		X				
Hopkins Verbal Learning Test (HVLT)		X				X
Patient-Reported Outcomes Measurement Information System (PROMIS)		X				X
Menstrual History Questionnaire [81]		X				
International Physical Activity Questionnaire (IPAQ)		X				
Pittsburg Sleep Quality Index (PSQI)		X				X
Verbal Fluency		X				X
Mediterranean Diet Adherence		X				
Trail Making Test (TMT) A and B		X				X
Magnetic Resonance Imaging		X				X
Electroencephalography		X				X
Balance Error Scoring System (BESS)		X				X
Cardiorespiratory Fitness Test		X				X
Actigraphy		X		X	X	

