### Study assessments

2.13

See Table 2 for complete schedule of all study assessments.

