### Intervention

2.14

All participants will engage in staff-led virtual exercise interventions three times a week for 30-min (5-min warm up, 20-min of aerobic/balance exercises, 5-min cooldown) for 12 weeks, making a total of 36 intervention sessions. Three sets of five exercises with modifications per each exercise have been developed for each intervention group (balance and aerobic) to help maintain engagement and allow intensity of the exercise to progress (see Table 3). Participants are seen individually for intervention sessions to ensure the research team can individualize exercise guidance and for safety monitoring All virtual sessions will be administered by two trained research staff members, one who leads the exercise session and one safety observer, monitoring safety. Heart rate (HR) will be monitored and recorded by hyperate4health (https://hyperate4health.netlify.app/), a proprietary open access platform and participants will be asked to rate their symptoms and exertion every 5 min. By collecting symptoms, HR using a Polar chest strap, and RPE every 5 min, we are directly targeting key limitations in other aerobic exercises studies done in TBI populations [18]. Aerobic sessions have a goal of reaching 20 min of aerobic exercise performed at 80 % of HR at symptom threshold. If this intensity increases symptoms by +3 on the symptom checklist, a 1-min break is taken, and the goal is reduced to 60 % of symptom threshold HR. If this intensity still exacerbates symptoms, another 1-min break is taken, and exercises will be done with a goal of 40 % of symptom threshold HR. Virtual aerobic exercises have been developed by an American College of Sport's Medicine certified Exercise Physiologist (JC) with experience delivering virtual aerobic interventions in older adults [83]. All participants are given a Polar HR strap and instructions on how to connect to HypeRate via Bluetooth to monitor their HR. Participants in the balance group are sent home with a foam pad to engage in non-aerobic physical activity like balance exercises. Each exercise is progressive in nature and includes modifications. All balance exercises were developed by a physical therapist (JM) and commonly used in clinical practice.

**Table 3 tbl3:** Intervention description.

Exercise description	Modification
Aerobic Version A	
Standing Twists w/Arm push	Normal, high arm, high arm with speed
Half Jacks	One arm, both arms, with jump
Imaginary Ball Slams	Normal, on toes, touch ground

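### The first accelerometer wear is in treatment week 1 in the Abstract and Fig. 1 but at Baseline in Table 2; on the week-1 version, change in daily activity has no pre-treatment reference

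*Protocol article*

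**What the plan says.** Four places in the protocol article bear on when the accelerometer is worn.

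- **Abstract:** "We implement physical activity monitoring during weeks 1, 6, and 12 using accelerometry to measure behavior changes".
- **Fig. 1 caption:** "Baseline is followed by 12-week intervention period with actigraphy at Week 1, Week 6, and Week 12".
- **Section 1.1, final exploratory aim:** change in "objectively measured daily physical activity and sedentary behaviors measured three times across the intervention period", to be related to neurological and cognitive outcomes. No week is named.
- **Table 2 (section 2.11):** the actigraphy row has three marks, under Baseline (in person), Week 6 and Week 12. The table has no Week 1 column. Section 2.13 gives the table its status: "See Table 2 for complete schedule of all study assessments".

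Section 2.5 fixes the order of events: "Participants are randomized after the baseline session is complete". Section 2.12 describes the device, the wrist placement and the sleep and removal log, but does not say when the wear periods fall. Section 2.14 sets the supervised load in both arms: "three times a week for 30-min (5-min warm up, 20-min of aerobic/balance exercises, 5-min cooldown) for 12 weeks".

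**The concern.** The article gives two schedules that cannot both be followed. They differ in the measurement that matters most to an aim about change, namely the reference value. In Table 2 it is taken before randomization. In the Abstract and Fig. 1 it is taken after the programme has begun.

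If the week-1 version is followed, three things are lost.

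- No accelerometer value precedes treatment, so a participant who becomes more (or less) active on starting the programme has that shift built into the reference.
- Nothing else listed replaces it. The IPAQ is given at baseline only, and the modified version described in section 2.11 asks about activity before the injury.
- Section 2.6 measures cognition at baseline and endpoint. Relating that change to activity change from week 1 to week 12 would pair a change that starts before treatment with one that starts after it.

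A secondary matter is that the wear weeks inside the intervention period also contain the study's own exercise sessions, while a pre-treatment wear would not.

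**Working it through.** **1. The schedules side by side**

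| Source | First wear | Second | Third | Is the first wear before treatment? |
|---|---|---|---|---|
| Abstract | Week 1 | Week 6 | Week 12 | No |
| Fig. 1 caption | Week 1 | Week 6 | Week 12 | No |
| Section 1.1 | three wears within the intervention period | | | No, by implication |
| Table 2 | Baseline | Week 6 | Week 12 | Yes (section 2.5) |

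The Table 2 row was aligned to its header column by column, and the marks fall on Baseline, Week 6 and Week 12. Section 1.1 fits only the week-1 version, because Table 2 places just two wears inside the intervention period. It does not itself say week 1, so the explicit conflict is two places against one.

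**2. The supervised load**

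Inputs from section 2.14: 3 sessions a week, 30 min each, 20 min of it the main block, 12 weeks.

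- Weekly total: 3 × 30 = 90 min, which reproduces the Abstract's figure.
- Sessions: 3 × 12 = 36, which reproduces section 2.14.
- Daily average: 90 / 7 = 12.9 min/day.
- Main block: 3 × 20 = 60 min/week, and 60 / 7 = 8.6 min/day.

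**3. What each schedule's change score contains**

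Write the recorded activity at time *t* as M(t) = D(t) + S(t), where D is activity outside sessions and S is activity recorded during sessions. Before treatment S(0) = 0.

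- Table 2 version: M(12) − M(0) = [D(12) − D(0)] + S(12).
- Week-1 version: M(12) − M(1) = [D(12) − D(0)] − [D(1) − D(0)] + [S(12) − S(1)].

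The week-1 version subtracts the initial uptake D(1) − D(0). If activity outside sessions rises in week 1 and stays there, the change score shows none of it, and no later analysis can recover it.

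The Table 2 version keeps the uptake but adds S(12) in full unless session time is removed. Over all session minutes S(12) is at most 12.9 min/day, and over the main block at most 8.6 min/day. In the week-1 version the session terms largely cancel, apart from differences in attendance and progression.

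**The case against.** **The conflict may be one of labels.** Section 2.12 implies wear at home over several days, so a mark under an in-person visit cannot be the wear period itself. It could mean that the device is handed out at baseline and worn in week 1. The article does not say this, and it does not say that wear ends before randomization either. The possibility stands, but it is a reason to clarify. If it is what was meant, the aim has no pre-treatment value.

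**A reader might infer that supervised sessions are counted as daily activity, and that this is a fault of the week-1 schedule.** The documents do not support that. No exclusion rule is stated, but a condensed article can leave such processing to a full protocol or analysis plan. Step 3 also shows that session time enters the change score mainly under the Table 2 schedule.

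**A reader might also take 8.6 min/day as the spurious gap between arms.** It is a ceiling. It needs full attendance, every aerobic main-block minute scored as moderate-to-vigorous, and no balance minute so scored. Section 2.14 targets 80 %, 60 % or 40 % of the symptom-threshold heart rate, and the test in section 2.7 stops by 85 % of age-predicted maximum. The targets are therefore at most 0.80 × 85 = 68 %, 0.60 × 85 = 51 % and 0.40 × 85 = 34 % of that maximum, and some sessions may not score as moderate-to-vigorous. The device is worn on the wrist, and the balance sets include arm movement and marching, so some balance minutes may register. Nor would the data miss behaviour outside sessions: sessions fill 90 of 10,080 min a week (0.9 %), and at least four days a week can be free of them.

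**The stakes are limited.** This is the last exploratory aim of a feasibility pilot that draws no inference from p-values, and no sample size depends on it.

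**Conclusion.** The contradiction is real and does not come from how the table was read. The Abstract and Fig. 1 place the first wear in treatment, section 1.1 is consistent with them, and Table 2 places it at Baseline. If weeks 1, 6 and 12 are followed, the aim of measuring change in daily activity has no pre-treatment device value and its window does not match that of the cognitive outcomes.

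The session-time point is secondary and holds only in a limited form. Weeks 6 and 12 carry up to 12.9 min/day of supervised sessions that a pre-treatment wear would not. The effect of this on the difference between arms is an assumption: in moderate-to-vigorous minutes it could run from nil, if both arms' sessions register alike, to 8.6 min/day from the main block under the extreme conditions above.

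Severity is minor to moderate. The schedule mismatch is certain. Which schedule is being followed in practice cannot be told from the article.

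**What to change.** 1. **Reconcile the schedule.** Make the Abstract, the Fig. 1 caption, section 1.1 and Table 2 agree, with the first wear completed before the first session, as the Table 2 Baseline mark implies, followed by weeks 6 and 12. State this timing in section 2.12. Cost: wording, and up to one week between the baseline visit and the first session (assuming a wear of about a week, since the article gives no length).
2. **Label data already collected.** Recruitment appears to be under way, so classify each first wear by its dates relative to the first session. Where only a week-1 wear exists, call it on-treatment and compare the arms at each week instead of reporting change from baseline. Cost: one derived variable.
3. **Report activity with session windows excluded, alongside the total.** This matters most once the reference is pre-treatment, because session minutes then enter the change directly. Sessions are staff-led and heart rate is recorded during them, so session times should be recoverable, although the article does not say that start and stop times are kept. Cost: a filter in the accelerometer processing.
4. **If week 1 was intended,** add a Week 1 column to Table 2, move the mark, and reword the aim as change during the programme, so that it is not read as change from a pre-treatment level.

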## Introduction

1

Mild traumatic brain injury (mTBI) represents one of the most prevalent neurological conditions, affecting an estimated 60 million individuals worldwide annually [1]. mTBI is not limited to sport related injuries but affects the population at large, and not all individuals make a complete recovery [2,3]. Moreover, cognitive impairment specifically is a significant predictor of returning to work after injury [4], yet there is no FDA-approved treatment available to directly treat cognitive dysfunction after an mTBI, making the clinical management of mTBI particularly challenging [5]. Current clinical practice rely primarily on symptom management and activity modification, with limited evidence-based interventions available to promote active recovery and functional improvement [5]. The widespread nature of mTBI, combined with the significant percentage of patients experiencing persistent symptoms, creates an urgent public health need that current approaches fail to adequately address. This treatment gap highlights the need for accessible, cost-effective, and scalable non-pharmacological interventions that can be widely implemented to support the substantial population of individuals experiencing persistent post-concussive symptoms and cognitive deficits. Given these challenges in mTBI management, aerobic exercise emerges as a promising therapeutic modality that improves cognition and overall brain health in the general population [[6], [7], [8]], targeting the underlying neurobiological mechanisms (i.e., axonal damage, neuroinflammation) contributing to cognitive dysfunction following mTBI.

Multiple systematic reviews have summarized the effects of physical activity and aerobic exercise on TBI outcomes in humans [[9], [10], [11], [12], [13], [14], [15], [16]], but findings are inconsistent due to significant methodological heterogeneity, such as inadequate control groups, intervention timing, outcome measures, and study populations. These methodological shortcomings reveal the critical need for rigorously designed randomized controlled trials that employ standardized, evidence-based exercise protocols, with appropriate active control conditions, to establish definitive clinical guidelines for exercise prescription in mTBI recovery. Additionally, prior interventions were delivered in person [[17], [18], [19], [20], [21], [22],[22], [22], [23], [24]] or unsupervised [[25], [26], [27]], limiting the scalability and accessibility to the intervention. Individuals recovering from mTBI encounter multifaceted barriers to physical activity participation that extend beyond the injury itself. Traditional in-person exercise programs may be particularly challenging for this population due to symptom exacerbation from travel, sensory sensitivities in gym environments, cognitive demands of navigating unfamiliar spaces, and executive function capacity required to coordinate going to an in-person exercise intervention. Virtual exercise interventions addresses these limitations, having demonstrated effectiveness and feasibility across diverse populations facing similar accessibility challenges, including individuals in rural communities with limited healthcare access and cancer survivors managing treatment-related fatigue and mobility restrictions [[28], [29], [30], [31], [32], [33], [34], [35]].

Here, we developed and will test an individualized, supervised, virtual, symptom-thresholded aerobic exercise intervention that directly addresses several barriers to participation by providing personalized, home-based exercise delivery that adapts to participants' fluctuating symptoms while accommodating for their unique schedules and environments. This approach eliminates transportation barriers while allowing real-time modification of exercise intensity based on symptom presentation. This protocol leverages previously established exercise tolerance tests, such as the Buffalo Concussion Treadmill Test [36], which have demonstrated validity in sport related concussion and in community dwelling individuals with mTBI [37,38]. While these tests have traditionally guided return-to-play for athletes, our approach applies this methodology specifically to non-sport related concussion and guides real-time engagement in physical activity interventions rather than serving as only a single use determinant for unrestrained and higher-risk activity. This individualized approach minimizes the risk of symptom exacerbation while fostering self-efficacy and confidence in physical activity engagement to promote lifelong engagement, particularly important for exercise-naïve individuals who may harbor concerns about their physical capabilities following brain injury.

The complex pathophysiology of TBI involves both immediate damage to the brain and prolonged secondary injury cascades, including neuroinflammation, oxidative stress, and disrupted cerebral metabolism [39,40]. These processes alter brain structure and function [[41], [42], [43], [44], [45], [46], [47], [48], [49], [50]], impeding natural recovery mechanisms, and create an urgent need for interventions that can counteract these detrimental effects. Emerging evidence suggests that physical activity and exercise may serve as a therapeutic tool by targeting multiple aspects of TBI pathophysiology simultaneously. In preclinical models, aerobic exercise demonstrates neuroprotective and neurorestorative properties, mitigating neuroinflammation, enhancing neurogenesis, and promoting synaptic plasticity [[51], [52], [53], [54], [55], [56], [57]]. Despite compelling animal model research on the neural responses to exercise following TBI, current clinical work primarily focuses on symptom improvement without addressing underlying neural damage [[58], [59], [60]]. Promoting recovery mechanisms in people recovering from TBI could directly address the secondary injury mechanisms that perpetuate persistent cognitive dysfunction following mTBI. By employing PA, it is our objective to bolster endogenous recovery mechanisms and directly counteract secondary injury mechanisms that perpetuate persistent cognitive dysfunction following mTBI.

Multimodal neuroimaging is also crucial for improving the understanding of exercise's mechanistic effect on TBI as it can capture the neural responses demonstrated in prior preclinical models [61]. Comprehensive imaging is particularly valuable given that exercise appears to affect multiple neural substrates simultaneously, suggesting a common underlying mechanism rather than isolated effects [49,62,63]. By using complementary imaging modalities, we can develop models of exercise induced recovery in mTBI, identify biomarkers for personalized exercise interventions, and bridge the translational gap between promising animal findings and human clinical applications. This would allow for TBI management to transform from a symptom management approaches to treatments that directly address the underlying neural injury while simultaneously treating symptoms in combination.

In 2022, The Lancet published key messages and recommendations for the future of TBI research [1]. Specifically, Table 1, section 3 called for improved access to rehabilitation services and develop evidence-based treatments for long-term problems, including fatigue, and cognitive and behavioral change [1]. This proposed study has the potential to improve accessibility to rehabilitation services and significantly contribute to the development of evidence-based treatment for cognitive problems. Thus, it is well posed to have a sizable impact on substantial gaps in the current literature, providing the basis for clinical care and future recommendations.

**Table 1 tbl1:** Inclusion-Exclusion Criteria for study participants.

Inclusion	Exclusion
Clinical diagnosis of mTBI (<1 year)	Diagnosis of moderate/severe TBI; history of mTBI > 1year
18–55 years of age	Presentation of skull breach or subdural hematoma
People of all gender identities, ethnicities/races, and socioeconomic status	Prior diagnosis of cognitive or physical disability
Ability to provide informed consent	Clinical diagnosis of other neurological or neuropsychiatric disorder
Safe to exercise (based answering “no” to all questions on the Physical Activity Readiness Questionnaire (PAR-Q))	Treatment for congestive heart failure, angina, uncontrolled arrhythmia, or other cardiovascular events
Normal or corrected to normal vision	History of myocardial infarction, coronary artery bypass grafting, angioplasty, or other cardiac condition in the last year
Able to speak, read, and write English	Regular use of assisted walking device
Ambulatory without pain or assistance of walking device	Not fluent in English
No diagnosis of comorbid neurological condition	Not medically cleared for exercise
MRI compatible (no metal or contraindications)	Not MRI compatible
No history of brain bleeds	

